## Abstract

**Background:**

Schizophrenia is a high-cost, chronic, serious mental illness. There is a clear need to improve treatments and expand access to care for persons with schizophrenia, but simple, tailored interventions are missing.

**Objective:**

To evaluate the impact of tailored mobile telephone text messages to encourage adherence to medication and to follow up with people with psychosis at 12 months.

**Methods:**

Mobile.Net is a pragmatic randomized trial with inpatient psychiatric wards allocated to two parallel arms. The trial will include 24 sites and 45 psychiatric hospital wards providing inpatient care in Finland. The participants will be adult patients aged 18–65 years, of either sex, with antipsychotic medication (Anatomical Therapeutic Chemical classification 2011) on discharge from a psychiatric hospital, who have a mobile phone, are able to use the Finnish language, and are able to give written informed consent to participate in the study. The intervention group will receive semiautomatic system (short message service [SMS]) messages after they have been discharged from the psychiatric hospital. Patients will choose the form, content, timing, and frequency of the SMS messages related to their medication, keeping appointments, and other daily care. SMS messages will continue to the end of the study period (12 months) or until participants no longer want to receive the messages. Patients will be encouraged to contact researchers if they feel that they need to adjust the message in any way. At all times, both groups will receive usual care at the discretion of their team (psychiatry and nursing). The primary outcomes are service use and healthy days by 12 months based on routine data (admission to a psychiatric hospital, time to next hospitalization, time in hospital during this year, and healthy days). The secondary outcomes are service use, coercive measures, medication, adverse events, satisfaction with care, the intervention, and the trial, social functioning, and economic factors. Data will be collected 12 months after baseline. The outcomes are based on the national health registers and patients’ subjective evaluations. The primary analysis will be by intention-to-treat.

**Trial Registration:**

International Standard Randomised Controlled Trial Number (ISRCTN): 27704027; http://www.controlled-trials.com/ISRCTN27704027 (Archived by WebCite at http://www.webcitation.org/69FkM4vcq)

## Introduction

Schizophrenia is a high-cost, chronic, serious mental illness [1]. The global prevalence of schizophrenia is about 1%-1.5% [2]. Among mental, neurological, and substance use disorders, schizophrenia is the third highest in the ranking of global burden in disability-adjusted life years [3]. Studies have shown that a prevalence among relapsed patients varies, for example from 52% [4] to 80% within 5 years [5]. Nonadherence to antipsychotic medication is highly prevalent, has a deleterious impact on the course of the illness [6], and is the single most important predictor of relapse and readmission [7], with all the subsequent costs being an additional burden [8-11]. People may be nonadherent to prescribed medications for many reasons. Forgetting to take the medication, feeling that it is unnecessary, and disliking adverse effects are all common [12]. In any event, it is probably an underestimate of real life that over half of people with schizophrenia stop medication within 1 year of discharge from hospital [13]. Individually tailored approaches to encourage adherence to medication have been called for [6].

Although simple and direct telephone calls [14-17] and well-timed prompting letters [18] may decrease nonattendance at psychiatric outpatient departments, short message service (SMS) with mobile phones may provide better access to a population group. Text messaging is common, inexpensive, and less intrusive than a phone call. It is also possible to send preprogrammed batches of messages. A trust-wide survey in the United Kingdom with 141 psychiatric inpatients (100 patients with psychotic illness and 41 who had a diagnosis of a nonpsychotic illness) showed that 55% had a mobile phone, 56% were able to use text messages, and 76% were willing to receive text messages from the National Health Service foundation trust [19]. We know of no similar data in Finland. In 2011, however, 98% of Finnish households had mobile phones, and about 20% had more than one mobile phone [20].

While there is a clear need to improve treatment and expand access to care for people with schizophrenia, mobile technologies could be developed to support this area [3]. As preparation for this trial, we are completing a Cochrane review [21]. We have identified relevant important pioneering work that has been reported in international conferences [22,23] (n = 865). There are already some applications in other areas of heath care. SMS has been used in asthma care [24], smoking cessation [25], promoting safer sex and sun safety in young people [26], and monitoring and coaching persons with chronic migraine [27]. People with schizophrenia or similar illnesses are, however, different from the standard health service population. SMS, if tailored and used sensitively, has the potential to be both potent and possible to implement in everyday care. To justify this, however, and not simply impose one more unevaluated intrusion into the lives of people with these disturbing illnesses, high-grade adequately powered data from randomized trials are required [6].

The Mobile.Net study will establish the impact of tailored mobile telephone text messages to encourage adherence to medication and to follow up with people with psychosis at 12 months. Mobile.Net is a short name for the trial to help health care professionals and participants be aware of the project.

## Methods

### Design

Mobile.Net is a multicenter, randomized controlled study with a two-armed trial conducted in Finland (24 sites and 45 hospital wards).

### Hypothesis

We hypothesized that tailored mobile telephone text messages acceptable to the individual patient would reduce use of services by people with serious mental illness whose previous use of services has been high.

### Inclusion and Exclusion Criteria

Inclusion criteria are patients aged 18-65 years, of either sex (Table 1), with antipsychotic medication [28] on discharge from a psychiatric hospital, who have a mobile phone, are able to use the Finnish language, and are able to give written informed consent to participate. We will include no formal test of capacity but will rely on the judgment of experienced health care professionals in their routine assessment, when nearing the point of discharge, of the patients’ understanding, retention, assimilation, and communication of all information, including that relevant to the study. Further formalized assessment is not part of routine care.

Patients who have planned a nonacute treatment period or are being treated in forensic psychiatric services will be excluded.

**Table 1 table1:** Dummy table for background characteristics in intervention (short message service) and control groups at baseline.

Characteristic		Intervention		Control	
		n	%	n	%
Age (years)		DUMMY TABLE - CELLS INTENTIONALLY EMPTY			
**Sex**					
	Male				
	Female				
	Other				
**Marital status**					
	Single				
	Married				
	Divorced				
	Widowed				
**Vocational education**					
	None				
	Vocational training courses				
	Primary vocational skill certificate				
	Secondary vocational skill certificate				
	University degree				
**Employment status**					
	Employed				
	Retired				
	Self-employed				
	Student				
	Job seeker				
**Number of previous psychiatric treatment periods**					
	1				
	2 or more				
Age at first contact with psychiatric services (years)					

### Interventions

#### Intervention Group

The intervention group will receive semiautomatic SMS messages after their discharge from psychiatric inpatient care. The intervention is patient led rather than researcher led to increase acceptability of the prompt. Therefore, during the discharge process from psychiatric hospital care, patients will choose text message content areas related to their medication and follow-up appointments. Additionally, they will be able to choose messages related to other daily issues (eg, hygiene, physical exercise, nutrition, daily routines, clothing, safety, communication, taking care of pets, following rules, hobbies, work or other activities, household tasks, symptom management, or other supporting messages). Timing, frequency, and conditions under which interventions will be withheld will be decided by the patient. The content of these messages had been designed by patients in a consumer association, and by health care professionals in hospital wards and outpatient clinics. The SMS messages will continue for the duration of the study period (12 months) or until participants no longer want to receive the messages. We do not envisaged that the intervention will interfere in any way with routine outpatient care. Patients will be encouraged to contact the researchers or health care staff if they feel that they need any adjustment of the message.

#### Control Group

Patients in the control group will receive standard treatment care in an outpatient unit based on the existing system in Finland.

All patients will receive usual care at the discretion of their team (psychiatry and nursing).

### Randomization and Masking

The randomization codes (permuted block design with 4 patients per block) were computer generated by an independent statistician. Others, completely independent of the trial team, inserted these numbers into sealed envelopes. While this is a multicenter study to be run in 24 sites—that is, health service organizations (and 45 study wards) with psychiatric beds in Finland—patients within each ward will be randomly allocated separately. The is an open-label study.

Written allocation of assignment will be sealed in individual envelopes marked with study identification numbers, which will be distributed to all study wards. Research nurses on study wards will sequentially assign sealed envelopes in a predetermined order to patients who fulfill the inclusion criteria and give their written informed consent during their discharge process. Investigators will be masked to data until the statistician releases the database, although a data management committee will undertake ongoing safety surveillance. Study participants and staff will not be masked; this would not reflect real-world care. However, randomization and analyses will be undertaken by investigators masked to treatment allocation.

The sealed envelopes with study identification numbers will be opened by a research nurse or a patient in an ascending manner. Patients will be allocated to the intervention or control group.

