### Allocation Concealment

Participants and the investigators enrolling the participants will not foresee assignment. We will use numbered sealed envelopes in different data collection organizations. Whereas patients and health care staff will be aware of the allocated arm, outcome assessors and data analysts will be kept blinded to the allocation.

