### Ethics Issues

The Ethics Committee of the Hospital District of Southwest Finland approved the study on December 16, 2010 (ETMK 109/180/2010). Any regulations addressing the conduct of trials involving vulnerable populations and clinical trials investigating products will be taken into account [37].

We did will not use any formal tests of capacity to evaluate patient competence. We will rely on the judgment of experienced health care professionals in their routine assessment of patients’ status and well-being. Study participants and staff will not be masked (blinded), so as to reflect real-world care. This may, however, cause ethical and practical outcomes. Participants may respond better if they know they have received a promising new treatment or worse if they received only standard care. Nurses may motivate patients more toward a specific group depending on which group (intervention or control) nurses prefer [38].

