### Recruitment Schedule

Recruitment started in November 2011 and will finish December 2012. Results will be reported in 2015.

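### Fixed blocks of 4 within each ward of an open-label trial leave up to one third of allocations deducible, so the design does not deliver the stated concealment

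*Protocol article*

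**What the plan says.** Under Randomization and Masking, the protocol article states that "The randomization codes (permuted block design with 4 patients per block) were computer generated by an independent statistician". It gives one block size and no variation. The same section says that "patients within each ward will be randomly allocated separately", so each ward runs its own sequence; the Design section counts "24 sites and 45 hospital wards".

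The sequence is handled on the ward: "Research nurses on study wards will sequentially assign sealed envelopes in a predetermined order to patients who fulfill the inclusion criteria". The envelope is used once written consent is given, during discharge, and a nurse or the patient opens the envelopes in ascending order. The study is open label: "Study participants and staff will not be masked; this would not reflect real-world care".

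Allocation Concealment then asserts, without qualification, that "Participants and the investigators enrolling the participants will not foresee assignment". Ethics Issues concedes, while discussing the lack of masking, that "Nurses may motivate patients more toward a specific group depending on which group (intervention or control) nurses prefer".

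**The concern.** A sealed envelope hides one card. It does not stop someone working out that card from those already opened. Here the people who enrol patients also hold the ward's sequence and can see its history. With a constant block size, the end of each block is determined by its beginning.

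What is at stake is selection before randomisation. If the next arm is known when a nurse decides whom to approach, or whether to wait, the arms can differ in underlying admission risk. Intention-to-treat analysis keeps patients in the arm to which they were allocated, and register data protect outcome ascertainment. Neither corrects a difference in who entered each arm. The target effect is only 5 percentage points, so a small shift in case mix matters.

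**Working it through.** **Inputs.** Block size 4, run by ward, open label, sequential envelopes (Randomization and Masking); 45 wards (Design); 1511 per arm, 65% admission rate, 5-point reduction, 80% power, two-sided 5% (Sample Size and Power Calculations). The 2:2 split within a block is inferred from the equal arms.

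**The plan's own figure.** For 65% versus 60%:

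- Uncorrected: n = [1.96·√(2·0.625·0.375) + 0.8416·√(0.65·0.35 + 0.60·0.40)]² / 0.05² = 1471 per arm.
- With continuity correction: (1471/4)·[1 + √(1 + 4/(1471·0.05))]² = 1511 per arm.

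This reproduces the stated size. The total is 2 × 1511 = 3022.

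**Deducible allocations.** A 2:2 block has 6 equally likely sequences. An allocation is determined once one arm is used up in the block.

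| Position | Chance already determined | Chance best guess is right |
|---|---|---|
| 1 | 0 | 1/2 |
| 2 | 0 | 2/3 |
| 3 | 1/3 (first two match) | 1/3·1 + 2/3·1/2 = 2/3 |
| 4 | 1 | 1 |
| Mean | (4/3)/4 = 33.3% | (17/6)/4 = 17/24 = 70.8% |

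Unpredictable assignment would give 0% and 50%.

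**Scale.** 3022/3 ≈ 1,007 allocations. Per ward, 3022/45 ≈ 67 patients, of which about 22 are deducible. Incomplete last blocks change little: 32.3% to 33.3% for the ward sizes checked between 60 and 68 patients, and 26.7% for a ward of 10.

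**Possible bias (the risk gap is an assumption; the article gives none).** Let g be the difference in 12-month admission risk between patients steered to one arm and those steered to the other. If steering happens only at deducible positions, one third of each arm is affected, so bias = g/3.

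- g = 3 points: bias 1 point.
- g = 6 points: bias 2 points.
- g = 15 points: bias 5 points, the whole target, if every ward steers the same way. If only half the wards do, g must be about 30 points.

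If nurses also act on the best guess at position 2, the block contributes (1/3 + 1/3 + 1)·(g/2) over 2 patients per arm, so bias = (5/12)·g. The full 5 points then needs g = 12 in all wards.

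**Effect on the test.** With 1511 per arm and a 65% rate, SE = √(2·0.65·0.35/1511) = 0.01735.

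- A 2-point bias shifts the test statistic by 0.02/0.01735 = 1.15, and the two-sided false-positive rate rises from 5% to about 21%.
- A 1-point bias shifts it by 0.58, and the rate rises to about 9%.

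**Alternative schemes.** Fixed blocks of 6 or 8 leave 25% or 20% deducible. With sizes varying at random among 4, 6 and 8, a simulation (68 patients per ward, 1,500 replications, set of sizes known to the nurse but not their order) gave about 2.3% deducible. The best guess was still right about 68% of the time. Varying sizes removes nearly all certainty, but not all guessing.

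**The case against.** The one third is a ceiling. Reaching it needs a nurse who knows or infers the size, keeps an exact tally for the ward and knows where each block starts. The codes came from an independent statistician, and people outside the trial team filled the envelopes. A reader might infer that nurses did know a third of allocations; nothing in the article shows this. It also does not say the size was kept from wards, and the size could be inferred from past assignments.

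A reader might also infer that the block size was public while patients were being enrolled, because "Recruitment started in November 2011 and will finish December 2012". The tense suggests the text was written during recruitment, but it carries no publication date, so the point cannot rest on this.

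A third tempting reading is that modest steering could create or hide the whole effect. The arithmetic does not support it: a 12- to 15-point gap, steered the same way in all wards, is not modest. Partial distortion is the realistic risk.

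Some safeguards are real. The envelope is opened only after consent, so its contents cannot influence consent. Tying enrolment to discharge limits reordering of patients. The analysis of covariance planned under Statistical Tests could adjust for measured imbalance. None of these stops deduction before a patient is approached, and covariate adjustment does not reach unmeasured differences.

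Finally, the sentence on nurses' preferences describes a general open-label limitation. It shows that a motive is acknowledged, not that the next envelope can be anticipated.

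**Conclusion.** The concern holds as a statement about what the design permits. Fixed blocks of 4 by ward, with sequential envelopes and unmasked staff, are incompatible with an unqualified claim that enrollers cannot foresee assignment. Up to 33.3% of allocations (about 1,007 of 3,022) are deducible and about 71% can be guessed correctly. This assumes complete 2:2 blocks and a nurse who knows or infers the size and follows the ward's history.

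Whether this was exploited is unknown, and the size of any bias depends on an assumed risk gap. Gaps of 3 to 6 points would give a bias of 1 to 2 points, enough to distort a test aimed at 5.

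The Abstract can be read as allocating whole wards to arms. This point rests on Randomization and Masking, which allocates patients within wards.

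**What to change.** 1. **Unopened envelopes.** Have the independent statistician issue new ward sequences with randomly varying block sizes, and withhold the new sizes from wards until recruitment closes. The size of 4 is already in print, so only the new sizes can be protected. Cost: one logistics round to up to 45 wards, controlled renumbering so that part-used sequences are not mixed up, and slightly looser within-ward balance. If recruitment has closed, only items 2 and 3 apply.

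2. **Allocation Concealment.** Restate the section to say that envelopes concealed individual assignments, but that allocations made under fixed blocks of 4 were partly predictable. Cost: a text change.

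3. **Patients randomised under blocks of 4.** Reconstruct each patient's position from the ward and the order of opening. Compare baseline characteristics between arms at deducible versus non-deducible positions. Report a sensitivity analysis of the primary outcome that leaves out the deducible positions. Whether a position is deducible depends only on earlier allocations in the block, so this exclusion does not select on the patient's own arm or outcome. Cost: about 3022 × 2/3 ≈ 2,015 patients remain and the standard error rises by about √1.5 = 1.22, so this supports the main analysis and does not replace it. It also does not remove steering on guesses at position 2.

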### Statistical Analysis Plans

#### Sample Size and Power Calculations

The study has been powered for the primary outcome measure. We have systematically searched for but not found any directly relevant published work. In London, for example, 65% of potentially eligible people had been admitted to the hospital in the past 12 months [36]. Our aim in Finland will be to reduce use of acute care by at least five percentage points (a relative risk of 0.92). To do this with 80% power at a 5% 2-sided significance level, we would require 1511 participants in each of the two arms (Stata v10; StataCorp LP, College Station, TX, USA).

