#### Statistical Tests

The primary outcome will be relative risk of admission to psychiatric inpatient services (Table 2). Secondary outcomes will involve calculation of relative risk or mean differences and their corresponding 95% confidence intervals. To evaluate the clinical outcomes of the study, we will use both descriptive and inferential statistics. Descriptive statistics will be used to evaluate outcomes at the end point and differences between individuals and groups by exploratory analyses (chi-square tests, *t *test or Mann-Whitney *U *test, and nonparametric bootstrap methods for skewed cost data). The principal analysis will compare the primary and secondary outcome measures at 12 months comparing for baseline (preintervention) measures using analysis of covariance.

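### Patients are randomised within 45 wards, but the stated principal analysis names no ward term (a mild, conservative loss of precision), and the abstract misnames the randomised unit

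*Protocol article*

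**What the plan says.** **Randomised unit, Methods.** The Randomization and Masking section describes a "permuted block design with 4 patients per block" and says that "patients within each ward will be randomly allocated separately". The mechanics are also individual: "Research nurses on study wards will sequentially assign sealed envelopes in a predetermined order to patients". The Design section gives "24 sites and 45 hospital wards".

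**Randomised unit, abstract.** The Methods paragraph of the abstract describes "inpatient psychiatric wards allocated to two parallel arms", which read literally is a cluster design.

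**Sample size.** The Sample Size and Power Calculations section starts from the figure that "65% of potentially eligible people had been admitted to the hospital in the past 12 months". It aims for a reduction of five percentage points with 80% power at a two-sided 5% level, and arrives at 1511 per arm. It mentions no design effect.

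**Analysis.** The Statistical Tests section makes the relative risk of psychiatric admission the primary outcome. It lists chi-square, t, Mann-Whitney and bootstrap methods as exploratory. It then describes the principal analysis as a 12-month comparison by analysis of covariance using pre-intervention measures. Neither ward nor site appears.

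**The concern.** Two things do not fit together.

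First, blocking within ward forces the arms to be nearly equal in every ward, so differences in admission rate between wards largely cancel out of the treatment comparison. An analysis that ignores ward still counts those differences as noise. Its standard error is then larger than the design implies, and some of the precision gained by stratifying is lost.

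Second, the abstract and the Methods name different randomised units. The Publication Plan foresees publication alongside a Cochrane review and offers the data for prospective meta-analysis. Individually randomised and cluster-randomised trials are handled differently there, so the unit must be stated correctly wherever it appears.

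**Working it through.** **1. Reproduce the planned sample size.** Inputs from the sample size section: control risk 0.65, intervention risk 0.60 (five points lower), two-sided 5%, power 80%. The mean risk is 0.625.

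n = [1.960 × √(2 × 0.625 × 0.375) + 0.842 × √(0.65 × 0.35 + 0.60 × 0.40)]² / 0.05² = (1.342 + 0.575)² / 0.0025, which gives 1471 per arm.

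Continuity correction: (n/4) × [1 + √(1 + 4/(n × 0.05))]² = 1511 per arm.

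This matches exactly. The formula treats patients as independent: it has no design effect and no gain from stratification. It therefore agrees with the Methods and not with the abstract's sentence.

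**2. Variance under randomisation within ward.** Write the total outcome variance as p(1−p), of which a share ICC lies between wards. Equal arm sizes imply 1:1 allocation, so with blocks of 4 the arms in a ward can differ by at most 2 patients, and the between-ward share nearly drops out of the difference:

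- variance assumed by an unstratified test: 2p(1−p)/n
- actual variance: about (1−ICC) × 2p(1−p)/n

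Hence:

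- standard error too large by the factor 1/√(1−ICC)
- actual size = 2 × [1 − Φ(1.96/√(1−ICC))]
- power with ward ignored = Φ[(0.05 − 1.96 × SE_u)/SE_t]
- power with ward stratified = Φ[0.05/SE_t − 1.96]

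with SE_u = √(2 × 0.625 × 0.375/1511) = 0.01761 and SE_t = SE_u × √(1−ICC).

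Worked example, ICC 0.05: SE_t = 0.01761 × √0.95 = 0.01717. Ward ignored: (0.05 − 0.03452)/0.01717 = 0.902, power 81.6%. Ward stratified: 2.913 − 1.960 = 0.953, power 83.0%.

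| Assumed ICC | SE too large by | Actual size | Power, ward ignored | Power, ward stratified | Loss (points, unrounded inputs) |
|---|---|---|---|---|---|
| 0.01 | 0.5% | 0.049 | 81.1% | 81.4% | 0.3 |
| 0.02 | 1.0% | 0.048 | 81.3% | 81.8% | 0.5 |
| 0.05 | 2.6% | 0.044 | 81.6% | 83.0% | 1.3 |
| 0.10 | 5.4% | 0.039 | 82.3% | 84.9% | 2.6 |

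These powers carry no continuity correction, so they start just above 81% rather than at 80%.

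**3. Check by simulation.** 20,000 trials per scenario, 45 wards of 34 + 34 patients, beta-distributed ward rates, unstratified z test against Cochran-Mantel-Haenszel. Power was 81.5% against 81.6% (ICC 0.01), 82.0% against 82.4% (0.02), 82.3% against 83.4% (0.05) and 82.7% against 85.0% (0.10). Under the null, the unstratified test rejected in 4.9%, 4.5%, 4.6% and 4.3% of trials, and the stratified test in 5.0%, 4.7%, 5.1% and 5.3%. The Monte Carlo standard error near 5% is √(0.05 × 0.95/20,000) = 0.15 points. At ICC 0.10 the unstratified rate is somewhat above the formula's 3.9%; a separate run of the same size gave 3.8%. Direction and order of size are confirmed.

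**4. Effect on the estimate.** With equal arms in each ward, every Mantel-Haenszel weight is one half, so the stratified relative risk is Σx₁/Σx₀, which is the crude one. Stratification changes the standard error and hardly moves the estimate.

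**The case against.** The strongest reply is that the article never excludes ward. It condenses a fuller protocol, and adjustment for strata may stand in an analysis plan that is not shown. A relative risk is an effect measure that can be computed with or without stratification, and the chi-square, t and Mann-Whitney tests are labelled exploratory, so they say little about the primary model. This stands in part: it cannot be claimed that the trial will ignore ward. What remains is that the article does state what its principal analysis adjusts for, and the factor used to stratify randomisation is not there.

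The reply that the effect is small and in the safe direction also stands. At an ICC of 0.01 to 0.02 the loss is half a point of power or less. The calculation further assumes similar ward sizes, which the documents do not give.

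A reader might go further from the abstract and infer a badly underpowered cluster trial. The arithmetic is easy: 3022/45 = 67.2 patients per ward; at an assumed ICC of 0.02 the design effect is 1 + 66.2 × 0.02 = 2.32, leaving about 650 effective patients per arm and about 46% power. The documents do not support that reading. The blocks, the envelopes and the sample size all concern individual patients, and no section plans allocation of whole wards. The figure shows only why the sentence needs correcting.

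**Conclusion.** The point holds in a modest form. As published, the principal analysis omits the randomisation stratum, and if ward is indeed left out the analysis is slightly less precise than the design allows. The sizes in the table rest on an assumed ICC range and on roughly even recruitment across wards.

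A reader might infer from a mismatch between design and analysis that false positives become more likely. The opposite is true here: omitting a factor balanced by design makes the test conservative. The comparison stays valid, and no design effect is called for.

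The contradiction over the randomised unit is plain and needs no assumption. It is confined to one sentence of the abstract; the operative Methods text is clear.

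**What to change.** 1. State that the primary analysis is stratified by or adjusted for ward: for example a Mantel-Haenszel relative risk stratified by ward, or ward as a fixed or random effect in the relative-risk model. Apply the same principle to time to next hospitalisation (stratified by ward) and to the continuous outcomes (ward effect in the model).
2. Fix in advance a rule for sparse wards, such as pooling within site (24 sites), since a ward with patients in only one arm contributes nothing to a stratified estimate and a model with 45 fixed effects can be unstable.
3. Correct the abstract to say that patients are individually randomised, within inpatient psychiatric wards, to two parallel arms.

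The cost is a few lines of analysis wording and one corrected sentence. Sample size, recruitment and conduct do not change. The one small downside is the handling of sparse wards.
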